***CM – Child marriage**

**KMO – Kaiser-Meyer-Olkin test**

### Quantitative surveys

The quantitative component includes baseline and endline (10 months after the end of intervention) data collection from the same cohort of adolescent girls and separate cross-sectional samples of adult male and female community members in all 51 study villages.

#### Sample size

The sample size for the quantitative component was calculated based on the primary outcome ‘child marriage’ among girls aged between 12 years and below 16. The rate of CM for this age group was unknown. Thus, we assumed a 50% prevalence rate and considered a cluster size of 22 adolescent girls. A life skills intervention in Maharashtra, achieved 19% reduction in CM in the community [38]. Based on this, we assumed a 15% effect size and an Intra-Cluster Correlation of 0.05. Considering 5% significance level and 80% power we required 17 clusters per arm making the total number of clusters 51. Considering a 15% non-response/dropout rate the group size increased to 25 and total sample size increased to 1,275 girls. To assess social norms change we considered child marriage related social norms among the adult community members aged 25 or more as the primary outcome. Since the prevalence of CM related norms is unknown in the study villages, we assumed it to be 50%. Considering a 15% effect size, 5% significance level, 80% power and 5% non-response rate, we required 540 community members from 51 clusters. To ensure participation of both males and females we required six adult males and six adult females from each cluster.

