#### Recruitment of study participants and formation of groups

From the household enumeration data, a list of eligible girls and community members was prepared. Girls were eligible for the study if they were: i) aged 12-<16 years; ii) unmarried; and currently living in the study village. Adult males and females aged 25 or more and currently living in the study village were considered eligible to participate in the community survey.

Simple random samples of 29 eligible girls were drawn from each cluster. We oversampled the girls by 16% to achieve a group size of 25, considering the possibility of refusal. In addition, six eligible adult males and six eligible adult females were selected at random from each village for the community survey. In intervention clusters, the lists of selected girls were provided to the implementing organization, which then approached girls from the list of 29 in random order to invite them to participate in the TPI until they had enrolled the 25 target participants per cluster. These girls were then approached to participate in the study, specifically the baseline survey, by the research team. In control villages, and for the adult community samples in each cluster, the research team directly invited the randomly selected participants to enrol in the study during the baseline survey, administered the consent form and interviewed the individuals.

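### Twenty-five girls per cluster leave 21.25, not the planned 22, if 15% of the enrolled cohort is lost; 25 covers a 12% loss, with little effect on power

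*Protocol article*

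**What the plan says.** The Sample size section gives all the figures involved. For the starting point it says "we assumed a 50% prevalence rate and considered a cluster size of 22 adolescent girls". It adds "we assumed a 15% effect size and an Intra-Cluster Correlation of 0.05", and concludes "Considering 5% significance level and 80% power we required 17 clusters per arm making the total number of clusters 51". The allowance for losses follows: "Considering a 15% non-response/dropout rate the group size increased to 25 and total sample size increased to 1,275 girls". The inflation formula is not printed, and the 15% is a single combined rate that is not divided between refusal and later dropout.

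Two other sections bear on the reading. Under Recruitment of study participants and formation of groups, 29 girls are drawn per cluster: "We oversampled the girls by 16% to achieve a group size of 25, considering the possibility of refusal". Under Quantitative surveys, the girls are a closed cohort; baseline and endline are described as "data collection from the same cohort of adolescent girls".

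**The concern.** An allowance for losses is meant to leave the number that the power calculation needs once those losses have happened. Here that number is 22 girls per cluster. Taking 15% from 25 gives less than 22, so the cluster size, the loss rate and the enrolled size cannot all stand together if the rate applies to enrolled girls.

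The loss rate matters to a reader because the girls are followed for a long time. Baseline ran from February to April 2019 and endline from November 2021 to January 2022, roughly 31 to 35 months apart. Anyone comparing actual attrition with the plan will use the 15% figure as the benchmark. With attrition of 13% to 15%, that reader would wrongly conclude that the planned 22 per cluster had been kept. What is at stake is the accuracy of a stated tolerance; the number of clusters is not in question.

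**Working it through.** **Inputs, all from the Sample size section.** Cluster size 22; 17 clusters per arm, 51 in total; prevalence 50%; effect 15%; intra-cluster correlation 0.05; significance level 5%; power 80%; loss 15%; enrolled size 25 per cluster and 1,275 in total.

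**Assumptions.** The 15% effect is read as absolute (50% against 35%). A relative reading (50% against 42.5%) would need about 64 to 67 clusters per arm, so it does not fit 17. The test is taken as two-sided, because the article does not state sidedness.

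**1. Reproducing 17 clusters.**
- Unpooled sample size per arm without clustering: (1.96 + 0.84)² × (0.5 × 0.5 + 0.35 × 0.65) / 0.15² = 166.6 (with unrounded normal quantiles).
- Design effect at 22 per cluster: 1 + 21 × 0.05 = 2.05.
- Clusters per arm: 166.6 × 2.05 / 22 = 15.52. Adding one cluster (the Hayes-Bennett form) gives 16.52, rounded up to 17.
- The continuity-corrected formula needs 182.4 per arm, and 182.4 × 2.05 / 22 = 17.00. If 182.4 is first rounded up to 183, the result is 17.05, hence 18.

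More than one route therefore leads to 17, and the article does not say which was used.

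**2. Reproducing 25 and 1,275.**
- Multiplying: 22 × 1.15 = 25.3, which rounds to 25; 51 × 25 = 1,275.
- Dividing by the retained fraction: 22 / 0.85 = 25.88, which gives 25 only if it is truncated.

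**3. What 25 delivers.**
- At 15% loss: 25 × 0.85 = 21.25 per cluster.
- In total: 1,275 × 0.85 = 1,083.75, about 1,084, against 51 × 22 = 1,122. The shortfall is 38.
- Loss that 25 can absorb: 1 − 22/25 = 12%.
- Enrolment that keeps 22 at 15% loss: 22 / 0.85 = 25.88, so 26 (26 × 0.85 = 22.1), and 51 × 26 = 1,326.

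**4. Effect on power, 17 clusters per arm.** The design effect at 21.25 is 1 + 20.25 × 0.05 = 2.0125. The effective number per arm moves from 17 × 22 / 2.05 = 182.4 to 17 × 21.25 / 2.0125 = 179.5, a drop of 1.6%.

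| Formula | 22 per cluster | 21.25 per cluster |
|---|---|---|
| Normal, unpooled | 83.4% | 82.9% |
| Normal, pooled | 82.9% | 82.3% |
| t with 32 degrees of freedom | 81.1% | 80.5% |
| Continuity-corrected | 80.0% | 79.3% |

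Before rounding, each row falls by 0.6 to 0.7 percentage points.

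**5. Clusters required at 21.25.** With one cluster added: 166.6 × 2.0125 / 21.25 + 1 = 16.78, still 17. With the continuity correction: 182.4 × 2.0125 / 21.25 = 17.27, so 18.

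**The case against.** The best defence is that the 15% combines non-response with dropout, and that refusal is dealt with elsewhere. Twenty-nine girls are drawn to fill a group of 25, and the Challenges and limitations section says that girls found ineligible on age were replaced. If refusal accounts for about 3 of the 15 points, the remaining loss is about 12% and 25 girls suffice. This stands as a reason not to treat all of the 15% as attrition without saying so. It does not remove the conflict, because the article never splits the rate, and the Sample size section offers the step from 22 to 25 as the allowance for all of it. The draw of 29 fills the group to 25 and does not enlarge it, so later attrition still falls on 25.

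It can also be said that no formula is printed. That is correct. Multiplying by 1.15 is the best fit, but it remains an inference. The shortfall is the same whether 25 came from rounding 25.3 or from truncating 25.88.

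Finally, the consequence is slight. With an intra-cluster correlation of 0.05, power depends mainly on the number of clusters, and losing 0.75 of a girl per cluster changes little. This also stands.

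**Conclusion.** The stated figures conflict: 25 per cluster does not leave 22 after a 15% loss from the enrolled cohort. It leaves 21.25, and it covers a 12% loss. This rests on applying the whole combined rate after enrolment, which is how the Sample size section reads but which the recruitment section leaves open.

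A reader might infer that the trial is underpowered. The document does not support that. Power at 21.25 per cluster stays between 80.5% and 82.9% under three of the four formulas tried, and the formula that adds one cluster still asks for 17. Only the continuity-corrected version falls below 80%, to 79.3%, and nothing in the article shows that it was the formula used. These power figures depend on the two-sided test and the absolute 15-point effect assumed above.

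This is a minor correction to a stated figure. It changes no design choice, cluster count or analysis.

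**What to change.** Change one sentence in the Sample size section, in either of two ways:

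- State that 25 girls per cluster (1,275 in total) allow for a 12% loss after enrolment, with refusal before enrolment covered by the draw of 29.
- Keep the 15% rate, say that it leaves about 21 analysed girls per cluster, and give the power at that size with the formula and sidedness used.

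Either version should make clear whether the rate refers to refusal, later dropout or both. The cost is one reworded sentence and a slightly less favourable stated figure. Enrolment and endline data collection are already complete according to the Participants' timeline section, and no additional girls are called for.

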#### Impact evaluation analysis

Intention-to-treat analysis will be used for assessing the impact of the TP program. Thus, all the TP girls enrolled in TPI will be included in the analysis irrespective of their actual level of participation in the intervention activities. The impact of the TP program on primary outcome, child marriage will be assed using hazard ratio while the TP secondary outcomes will be assessed using risk ratios derived from binary regression analyses for measuring change in outcomes in the intervention arms relative to change in the control arm. Mixed-effects models will be constructed with clusters as random effects and time point, intervention group, and time point x intervention interaction as fixed effects. Adjusting for the dependent variables at baseline survey we will obtain a measure of the relative change in intervention group that took place between baseline and endline compared to the change in the control group. The background characteristics for which the differences between study arms are evident, the pre-existing differences will be controlled in subsequent analyses. All analyses will be adjusted for the potential factors associated with the outcomes of interest.

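### The adult norms sample was sized for a one-time comparison of two proportions, but the planned test is a difference in change between separate cross-sections, so power for 15 points is about 45–60%, not 80%

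*Protocol article*

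**What the plan says.** The Sample size section treats child-marriage norms among adults as the primary outcome for assessing norm change. It assumes a 50% prevalence and continues: "Considering a 15% effect size, 5% significance level, 80% power and 5% non-response rate, we required 540 community members from 51 clusters". It then fixes six men and six women per village, which is 12 × 51 = 612 per survey. It gives an intra-cluster correlation (0.05) for the girls' calculation and none for the adults.

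The Quantitative surveys section says the adult data at baseline and endline come from "separate cross-sectional samples of adult male and female community members in all 51 study villages". The adults are therefore not followed as a cohort, unlike the girls.

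The Impact evaluation analysis section assesses secondary outcomes, which in Table 1 include adult norms (outcome 10), by "measuring change in outcomes in the intervention arms relative to change in the control arm". The mixed model has clusters as random effects and "time point, intervention group, and time point x intervention interaction as fixed effects".

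**The concern.** The sample size and the analysis refer to different contrasts. The inputs to the adult calculation are one prevalence, one effect, a significance level, power and non-response. Nothing in them reflects a baseline survey whose sampling error must be subtracted out. A time-by-arm interaction carries that error in full when the two surveys interview different people, because no within-person correlation cancels it.

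This is separate from the missing design effect: the loss is present at an intra-cluster correlation of zero. A village random intercept removes variation between villages that is stable over time, but it does not remove the doubled person-level variance.

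Norm change is what separates TPP+ from TPP, and adult norms are the outcome the Sample size section chose for measuring it. If a true 15-point shift is missed about half the time, a null result would be read against a claimed 80% power that the analysis does not have.

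**Working it through.** **Inputs from the article.** Prevalence 50%; effect 15%; significance 5%; power 80%; non-response 5%; 540 adults (180 per arm); 12 adults per village; 17 villages per arm; intra-cluster correlation (ICC) 0.05, given for girls only.

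**Assumptions.** The effect is 15 percentage points and the test is two-sided; this reading reproduces 540. The 540 applies to each survey. True prevalence is 50% in both arms at baseline and in control at endline, and 35% or 65% in the intervention arm at endline. The adult ICC and the village autocorrelation between surveys are not given, so ranges are shown.

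**1. Reproducing 540.** For two proportions at one time point, with pooled variance under the null:

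n = [1.96·√(2·0.425·0.575) + 0.842·√(0.25 + 0.2275)]² / 0.15² = 169.3, so 170 per arm.

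170 × 3 / 0.95 = 537, against 540 stated.

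Other readings do not fit: a relative 15% effect gives 2,188, a one-sided test 423, and a design effect at ICC 0.05 with 10–12 adults per village 778–832.

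**2. Variance of the two contrasts** (n responders per arm per survey, no clustering):

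- Endline comparison: (0.25 + 0.2275)/n = 0.4775/n
- Difference in change: (3 × 0.25 + 0.2275)/n = 0.9775/n

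The ratio is 2.05.

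**3. Power for 15 points, no clustering.** Power = Φ(0.15/SE − 1.96).

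| Responders per arm per survey | Endline: SE, power | Difference in change: SE, power |
|---|---|---|
| 171 (180 less 5%) | 0.0528, 81% | 0.0756, 51% |
| 194 (204 less 5%) | 0.0496, 86% | 0.0710, 56% |
| 204 (12 per village, full response) | 0.0484, 87% | 0.0692, 58% |

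**4. On the planned risk-ratio scale, no clustering.** The log of the ratio of risk ratios has SE = √{[3 + (1 − p)/p]/n}, where p is the intervention endline prevalence.

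- p = 0.65: log ratio 0.262; power 45% at n = 171, 49% at 194, 51% at 204.
- p = 0.35: log ratio 0.357 in size; power 56%, 62% and 64%.

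**5. With clustering.** For m responders per village per survey and village autocorrelation c:

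Var = (0.9775/17) × [ICC(1 − c) + (1 − ICC)/m]

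At ICC 0.05:

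| Responders per arm per survey | c = 1.0 | c = 0.8 | c = 0.5 |
|---|---|---|---|
| 171 (m about 10) | 53% | 49% | 44% |
| 194 (m about 11.4) | 58% | 54% | 48% |
| 204 (m = 12) | 60% | 55% | 49% |

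At c = 0, power falls to 38–41%.

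**6. Detectable difference in change at 80% power** (2.80 × SE). Without clustering: 2.80 × 0.0756 = 21 points at 171 and 2.80 × 0.0710 = 20 points at 194. Over the clustered cases in step 5, about 19 to 23 points.

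**7. Size that would match the interaction.** (1.96 + 0.842)² × 0.9775 / 0.15² = 341 responders per arm per survey; 341 × 3 / 0.95 = 1,077 adults per survey before any allowance for clustering, against 612 planned.

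**8. Endline comparison adjusted for village baseline prevalence.** The endline variance, (0.4775/n) × [1 + (m − 1)·ICC], is multiplied by (1 − r²), where r = c·ICC·m/[1 + (m − 1)·ICC]. At 194 responders per arm (m about 11.4), ICC 0.05 and c = 1.0/0.8/0.5, r = 0.38/0.30/0.19 and power is 75%/73%/70%.

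**The case against.** The strongest counter-argument is that the Impact evaluation analysis section, just after naming the interaction, also speaks of adjusting for the outcome measured at baseline. Adults are not re-interviewed, so for them this could only be a village-level covariate, which is close to the better analysis in step 8. The section is therefore ambiguous, and this part of the objection stands. It does not rescue the stated power. The same sentence still defines the result as change relative to change in control, the interaction is the term explicitly named, and no village-level covariate is mentioned.

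The article also gives one generic model for all secondary outcomes and may leave its adaptation for adults to an analysis plan. But this is not a complaint about missing detail: the article states both a power and an analysis, and they disagree.

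Three further points are fair:

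- The planned number is 612 per survey, not 540. That raises power from 51% to 56–58% without clustering, which reduces the shortfall without removing it.
- Part of the gap in the clustered figures comes from the ICC: at 0.05 and 194 responders per arm, even an unadjusted endline comparison has only about 69%. The loss at ICC zero is due to the interaction alone.
- Table 1 lists adult norms as secondary and all three study objectives concern child marriage. The girls' calculation is not affected: at 50% against 35%, 22 girls per cluster and ICC 0.05, it needs 15.8 clusters per arm, and 17 were taken. The main child-marriage comparison is untouched.

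**Conclusion.** The concern holds. The total of 540 is correctly calculated for a comparison the analysis section does not plan. For the time-by-arm contrast it does plan, power to detect 15 points is 51% at 540 and 56–58% at 12 adults per village without clustering. At ICC 0.05 with village autocorrelation between 0.5 and 1.0 it is 44–60%. On the risk-ratio scale, without clustering, it runs from 45% to 64% depending on sample size and direction of effect. The detectable difference is about 19–23 points.

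The exact figures rest on the 15-point, two-sided reading, on 540 being a per-survey number, and on an adult ICC and autocorrelation the article does not supply. These affect the size of the shortfall, not its existence. The consequence is confined to the adult norms outcome, but there it is serious enough that the plan should be corrected before a null result is interpreted.

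**What to change.** No extra participants are needed. Choose one of two courses.

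1. **Preferred.** For adult norms, make the confirmatory contrast the endline comparison between arms, with a village random effect and the village's baseline norm prevalence as a village-level covariate. A constrained-baseline model (no arm difference at baseline, plus a village-by-time term) would serve equally. Drop the unconstrained interaction for this outcome and say explicitly that the baseline adjustment is at village level. Restate power as about 70–75% for 15 points at 12 adults per village and ICC 0.05. This still falls short of 80%, and the text should say so.
2. **If the interaction is kept,** restate its power as about 50–58% for 15 points, with a detectable difference of about 19–23 points, and report the assumed adult ICC and village autocorrelation.

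The cost is a change of wording and a less favourable power statement; the village baseline prevalences are already collected. Because the endline survey is complete and nobody was blinded to allocation, a change of confirmatory contrast should be dated and documented as made before adult results by arm were seen. If that cannot be shown, take the second course and report the adjusted endline comparison as supportive.

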### Secondary outcomes

Secondary outcomes measured are: (1) Intrinsic agency – defined as one’s consciousness of own aspirations, capabilities, and rights [51–53]; (2) Instrumental agency – defined as the action to achieve one’s aspirations and goals [51–53]; (3) Collective agency – defined as the collective action to achieve common goals [51–53]; (4) social norms – defined as the normative expectations and empirical expectations regarding child marriage, and girls’ ability to stand up for their rights [54,55].

The specific secondary outcomes of TP include: (1) Adolescent girl’s self-efficacy in achieving life goals and collective efficacy in preventing CM; (2) Adolescent girl’s aspiration about marriage and education; (3) Adolescent girl’s knowledge about Sexual and Reproductive Health and Rights; (4) Attitudes towards gender and rights among adolescent girls and adult community members; (5) Cohesion among adolescent girl; (6) Communication and negotiation skill of adolescent girls; (7) Adolescent girl’s mobility; (8) Participation in financial activities among adolescent girls; (9) Power relations between adolescent and parents; and (10) Perception of Social norms among adolescent girls and adult community members. The details of the study outcomes are presented in Table 1.

**Table 1. t0001:** Primary and secondary outcomes of the Tipping Point impact evaluation in Bangladesh

SL	Outcomes	Indicator/ domain	Target population	Measurement	Questions/Scale used	Number of items	Cronbach Alpha	KMO	Expected direction of change

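### The adult community sample of 540 contains no design effect although villages are randomised, so 80% power for a 15-point norm difference holds only if the adult intra-cluster correlation is very small

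*Protocol article*

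**What the plan says.** The Sample size section of the protocol article holds two calculations.

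- **Girls.** The prevalence is taken as 50% and the cluster size as 22. Then "we assumed a 15% effect size and an Intra-Cluster Correlation of 0.05". With 5% significance and 80% power this leads to 17 villages per arm.
- **Adults.** The sizing outcome is "child marriage related social norms among the adult community members aged 25 or more as the primary outcome". On prevalence: "Since the prevalence of CM related norms is unknown in the study villages, we assumed it to be 50" per cent. Then: "Considering a 15% effect size, 5% significance level, 80% power and 5% non-response rate, we required 540 community members from 51 clusters". No ICC, design effect or cluster size appears among the adult inputs. The section then sets six men and six women per village, which is 12 x 51 = 612 adults. The reason given is that both sexes should be represented.

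Elsewhere, Cluster selection and randomization makes the village the randomised unit, with 17 per arm. Recruitment of study participants draws the adults within those villages. Impact evaluation analysis plans mixed models with clusters as random effects. Secondary outcomes lists "Perception of Social norms among adolescent girls and adult community members" as item 10, and Table 1 also places adult norms under secondary outcomes, with child marriage as the only primary outcome.

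**The concern.** Adults in one village receive the same allocation and share a community, so their answers on norms will tend to be correlated. A required number that ignores this overstates the information in the sample. The same paragraph allows for clustering in the girls and not in the adults, under the same randomisation.

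Community norm change is the element that TPP+ adds to TPP, and the adult survey is its community-level measure. If the stated 80% is carried into the report, a non-significant adult result will look more informative than it is.

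Calling adult norms the primary outcome in the sizing paragraph, against the secondary listing elsewhere, adds a smaller ambiguity about how much weight that result should carry.

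**Working it through.** **Inputs from the Sample size section:** proportions 0.50 and 0.35 (0.65 gives the same answer); 5% significance, taken as two-sided; 80% power; 5% non-response. There are three arms of 17 villages.

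**Step 1: reproduce 540.** The two-proportion formula with pooled variance under the null is

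n = [1.96 x sqrt(2 x 0.425 x 0.575) + 0.842 x sqrt(0.25 + 0.2275)]² / 0.15² = 169.3, so 170 per arm.

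170 / 0.95 = 179 per arm, and 179 x 3 = 537. Rounded to 180 per arm this is 540. Variants:

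| Variant | Total over three arms |
|---|---|
| Unpooled variance, no design effect | 528 |
| Variance 2 x 0.25, no design effect | 552 |
| One-sided 5% | 426 |
| Continuity-corrected | 579 |
| Relative 15% (50% v 42.5%) | 2,190 |

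The stated figure therefore fits a 15-point absolute difference with a design effect of 1.

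**Step 2: compare the girls.** Design effect = 1 + (22 - 1) x 0.05 = 2.05. Villages per arm = 169.3 x 2.05 / 22 = 15.8; adding one village gives 16.8, which rounds up to the stated 17. Clustering is in that figure.

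**Step 3: power for adults with clustering.** With m respondents per village, the design effect is DE = 1 + (m - 1) x ICC and the effective number per arm is 17m / DE. Respondents per village after 5% non-response:

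- stated 540: 540 x 0.95 / 51 = 10.06
- fielded 612: 12 x 0.95 = 11.4

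The adult ICC is an assumption, so a range is shown. Power is for 50% v 35% by the normal approximation. Where two values appear, the lower uses the pooled and the higher the unpooled standard error.

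| Assumed adult ICC | DE, 540 | Power, 540 less 5% | DE, 612 | Power, 612 less 5% |
|---|---|---|---|---|
| 0.01 | 1.09 | 77-78% | 1.10 | 81-82% |
| 0.02 | 1.18 | 74% | 1.21 | 78% |
| 0.03 | 1.27 | 70-71% | 1.31 | 74-75% |
| 0.05 | 1.45 | 65% | 1.52 | 68-69% |
| 0.10 | 1.91 | 53-54% | 2.04 | 55-56% |

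Example for 612 at ICC 0.05: 17 x 11.4 / 1.52 = 127.5 effective adults per arm. Then 0.15 / sqrt(0.4775 / 127.5) - 1.96 = 0.49, and Phi(0.49) = 0.69. A t reference on 32 degrees of freedom lowers this to about 66%.

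**Step 4: the ICC at which 612 still gives 80%.** Solve 17m / DE = 169.3. With m = 11.4: ICC = (193.8 / 169.3 - 1) / 10.4 = 0.014. If all 612 respond (m = 12): ICC = (204 / 169.3 - 1) / 11 = 0.019.

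**Step 5: detectable difference at 80% power, 612 less 5%.** About 17 points at ICC 0.05. At ICC 0.10, about 19.5 points with the unpooled standard error, slightly more with the pooled one.

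**Step 6: the size of the gap at ICC 0.05 with 51 villages fixed.** At m = 19, DE = 1 + 18 x 0.05 = 1.90, and 17 x 19 / 1.90 = 170 effective adults per arm. That is 19 respondents, or 19 / 0.95 = 20 invited, per village: 20 x 51 = 1,020 adults.

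**The case against.** Several points on the other side stand.

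- **The adult ICC is unknown.** A reader might infer that true power is 65-69%. The article assigns 0.05 to child marriage in girls aged 12 to under 16, which is a different outcome and population. It gives no value for adult norms, so 65-69% is one row of a range. At ICC 0.01 the 612 adults do reach 80%. It follows that a one-in-three chance of missing a 15-point change is not established either.
- **540 is not what was fielded.** The power of the actual survey is the 612 column. The 540 column bears only on the stated claim.
- **The analysis respects clustering.** The planned models carry cluster random effects, so the fault lies in the stated power. It does not make the planned estimates or their intervals invalid.
- **The primary label has a mild reading.** In context it can mean the outcome used to size the community survey. A reader might infer a second primary trial outcome, but the Trial outcomes section and Table 1 do not support that.
- **Misreading of a null is a risk only.** Nothing in the article says that a null will be reported as absence of effect.

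A reader might also multiply the unclustered size by the present design effect, 169.3 x 1.52 / 0.95 x 3, and conclude that about 813 adults would have been enough. That holds only if villages are added. With 51 villages, 813 adults give about 15.1 respondents per village, a design effect of 1.71 and 75-76% power at ICC 0.05.

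Figures for each sex alone, or for the time-by-arm contrast, are not offered. The article plans no powered comparison by sex and gives no correlation between survey rounds.

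None of this restores the omitted design effect. The 12 adults per village are explained by representation of the sexes, and they secure 80% only for an ICC below about 0.014 to 0.019.

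**Conclusion.** Wrong as written, and a should-fix. That 540 leaves out clustering does not depend on any ICC assumption, because the figure is reproduced from the article's own inputs with a design effect of 1. The size of the power loss does depend on one. Over assumed ICCs of 0.01 to 0.10, the fielded 612 adults have about 82% down to 55% power for a 15-point difference, and the stated 540 about 78% down to 53%. At the girls' value of 0.05, borrowed as an assumption, the figures are 68-69% and 65%. They rest on 17 villages per arm of equal size, 5% non-response, an endline comparison of two arms and the normal approximation, with no gain counted from covariate adjustment. The outcome is secondary and the primary calculation for girls allows for clustering, so nothing more severe is warranted.

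**What to change.** Restate the adult calculation with a design effect and an ICC that is labelled as an assumption. For example: *With 612 adults (about 11.4 analysed per village), 17 villages per arm and an assumed ICC of 0.05 (design effect 1.52), the survey has 80% power for a difference of about 17 percentage points and about 68-69% for 15 points; at an ICC of 0.10 the detectable difference is about 19.5 points.* Showing the values at ICC 0.01 to 0.03 as well would make the dependence plain.

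Withdraw the unqualified claim of 80% power for 15%. Describe adult norms as the outcome that sizes the community survey and as a secondary trial outcome, in line with Table 1. State that a non-significant adult result will be interpreted through its confidence interval.

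The cost is wording and a less favourable stated power. Endline data collection ended in January 2022, and no extra respondents are proposed.
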